#### Secondary endpoints

The secondary endpoints include symptomatic recurrence rate (assessed by the Visick grading system [18]), symptoms related to treatment (fluid, pain, irritation, itch, burning), usage of pain medication and quality of life. These secondary endpoints are assessed by the patient. Some other secondary endpoints are measured by an assessor with an assessment form including anatomic recurrence of SPSD, time to wound closure (defined as the time from the day of surgery until the day of complete epithelialisation) and surgical site infection.

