## Background

Sacrococcygeal pilonidal sinus disease (SPSD) is an acquired disorder of the natal cleft. In patients with SPSD, there are one or more sinus openings in the natal cleft with a blind-ending subcutaneous sinus. It has a prevalence of 8.3% [1]. There is a sex preponderance in men presenting with SPSD between the age of 20 and 30 years [2]. Although 3.7% of patients do not have any symptoms (silent disease), SPSD may cause symptoms interfering with quality of life and social function [1]. Symptoms associated with SPSD are pain, itch and discharge from the sinus with soiling of the underwear. Moreover, infection of the sinus with abscess formation may develop. In patients with silent SPSD, watchful waiting should be the treatment of choice [3]. An abscess requires simple surgical drainage. For patients with complaints due to chronic SPDS interfering with normal daily life, however, several treatment options have emerged in the past years. Simple excision of the pit of the sinus according to Lord and Miller [4], radical excision of the sinus and unroofing of the sinus are frequently used treatment modalities for SPSD [5].

Radical surgical excision of the sinus with primary wound closure or secondary wound healing is the most frequently used treatment for chronic SPDS [4,6,7]. Surgical site infection (SSI), however, is a frequent complication of radical excision with prevalence up to 24% [2]. SSI leads to secondary wound healing which may take several months to cure [8]. The use of a gentamicin-absorbed collagen sponge on the sacrococcygeal fascia reduced the infection rate after primary closure from 20% to 5% in one study [9], although this difference could not be confirmed by another study (26% versus 22%) [10]. The relatively big surgical trauma and the high rate of wound complications after radical excision results in a long wound healing time (mean (standard deviation (SD)) of 15 (4.9) days) and a long mean time to return to normal activity (9.7 (3.6) days) [2,5]. The recurrence rate after excision of SPSD is another problem. Midline wound closure after excision of SPSD has a mean (SD) recurrence rate of 11.1% (0.81%). Off-midline wound closure (Karydakis flap reconstruction), however, possibly seems to decrease the recurrence rate to 4% [2,5].

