Another minimal invasive treatment modality for SPSD is excision of the pit(s) of the sinus followed by the applications of phenol into the sinus tract. Phenol has sclerosant properties destroying epithelium and debris in the sinus and is thereby able to promote healing of the sinus [11]. This procedure, first described in 1964, is performed in an ambulatory setting under local anaesthesia [12]. Other advantages of this treatment modality over radical surgical excision of SPSD are a smaller surgical wound with less pain and faster wound healing, and therefore faster recovery and return to normal activity. A disadvantage is the higher recurrence rate. A review of the literature in 2009 [13] reported a mean (SD) recurrence rate of 12.6% (0.91%) after follow-up of 2 years, but without results from randomised controlled trials. Therefore, some patients require another phenolisation treatment to cure the SPSD. The surgical site infection rate after phenolisation treatment was reported as 8.7%. The mean (SD) return to work after the procedure was within 2.3 (3.8) days [13]. Some other cohort studies have been performed since then showing a recurrence rate varying between 8.7 and 33.3% after a follow-up of 22 to 26 months. Mean wound closure time varied from 16 to 28 days, SSI from 0% to 8.7% and return to work from 0 to 3 days [11,14-16].

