### Participant timeline

Patients who meet the inclusion criteria will be randomly assigned to either group A (pit excision followed by phenolisation) or group B (primary surgical excision). Patients randomised to group A are treated with excision of the sinus pit and phenolisation of the sinus tract. Afterwards, patients enter into the follow-up programme. If there is recurrent anatomic SPSD combined with symptoms interfering with daily life after at least 6 weeks, the phenolisation procedure is repeated. The treatment in group A can therefore consist of up to two phenolisation sessions. Patients randomised to group B primarily undergo excision of the sinus. Afterward, patients enter into the follow-up programme.

Data regarding quality of life and complaints related to SPSD are obtained preoperatively by questionnaires. Furthermore, the number and locations of pits of the SPSD in the natal cleft are preoperatively assessed. After the procedure, patients enter the follow-up programme. This consists of a diary during the first 2 weeks after the intervention to score complaints related to the surgical intervention, usage of pain medication and loss of days to perform normal activity and, at 1, 2, 6, 12, 26 and 52 weeks after the surgical intervention, quality of life scores, complaints in the natal cleft, satisfaction assessment and wound assessment are measured.

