The wound is postoperatively assessed by an assessor with an assessment form. This form includes anatomic recurrence of SPSD, wound closure (defined as complete epithelisation of the skin) and surgical site infection scored by the Southampton wound scoring system [20]. This scoring system consists of six grades: normal healing (grade 0), normal healing with mild bruising or erythema (grade I), erythema plus other signs of inflammation (grade II), clear or haemoserous discharge (grade III), pus (grade IV) and deep or severe wound infection with or without tissue breakdown (grade V).

To encourage patients to complete follow-up, appointments are scheduled for all patients and a reminder is sent to them 2 to 3 days prior to the appointment.

All forms and questionnaires will be kept in locked cabinets and access to the study data will be restricted. All data will be entered electronically in a SPSS database (SPSS Inc., Chicago, IL, USA) and a password system will be utilized to control access and prevent unauthorised access.

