### Statistical methods

The analysis in this study will be performed according to the intention-to-treat principle; that is, all participants, regardless of protocol adherence, will be analysed as randomised [21]. Continuous variable will be summarised using mean (SD) or medians (interquartile range), and binary and categorical data will be summarised using frequencies and percentages, where appropriate. Data will be analysed using SPSS for Windows version 17.0 (SPSS Inc.). We will calculate relative risk and relative risk reduction with corresponding 95% confidence intervals to compare dichotomous variables. The paired-samples *t* test will be used for statistical analysis of continuous pre- and postoperative values and the *t* test for independent samples for statistical analysis of continuous values between both intervention groups. Statistical analysis of categorical values between both groups will be performed using the Pearson Chi-square test, and statistical analysis of categorical pre- and postoperative values by the McNemar test. Differences will be considered statistically significant with *P* < 0.05. We will report reasons for withdrawal for each randomisation group. The effect that any missing data may have on results will be assessed by sensitivity analysis [21,22].

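### Time to wound closure is defined to the day but the wound is assessed at widely spaced visits, so unless a closure date is obtained between visits it is interval-censored and the general t test does not suit it

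*Protocol article*

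**What the plan says.** All places are in the Protocol article.

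- **Definition.** Secondary endpoints includes "time to wound closure (defined as the time from the day of surgery until the day of complete epithelialisation". It belongs to the group introduced by "Some other secondary endpoints are measured by an assessor with an assessment form".
- **Visits.** Participant timeline places the follow-up measurements "at 1, 2, 6, 12, 26 and 52 weeks after the surgical intervention"; the list ends with "satisfaction assessment and wound assessment are measured".
- **Form.** Data collection says of the assessor's form: "This form includes anatomic recurrence of SPSD, wound closure (defined as complete epithelisation of the skin". This is a state (closed or not). No closure date is mentioned.
- **Diary.** The only daily instrument runs for two weeks. According to Participant timeline and Data collection it covers complaints, pain, pain medication and normal activity, not closure.
- **Expected values.** Background gives "a long wound healing time (mean (standard deviation (SD)) of 15 (4.9) days" for excision. For phenolisation it says "Mean wound closure time varied from 16 to 28 days", without an SD.
- **Analysis.** Statistical methods assigns the *t* "test for independent samples for statistical analysis of continuous values between both intervention groups". No separate method is named for time to wound closure.

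**The concern.** If an assessor learns whether the wound is closed only at a visit, closure is known to have happened after the last visit at which it was open and by the first visit at which it was closed. The gap between weeks 2 and 6 is 28 days wide, and it sits where the article expects closure. If the visit date is then taken as the closure date, wounds closing on day 15 and day 41 get the same value, while wounds closing on day 14 and day 15 differ by 28 days. A t test would treat these values as exact. It also has no value for a wound still open at the last visit, and Background itself says that healing after infection can take months.

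At stake are the reported days to closure and the difference between groups. Faster wound healing is one of the advantages the article attributes to phenolisation, so readers will look at this result.

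**Working it through.** The article gives no computed figure for this endpoint, so there is none to reproduce. The check asks what the stated visits would do to the stated closure times.

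**Inputs from the article.** Visits at weeks 1, 2, 6, 12, 26 and 52 are days 7, 14, 42, 84, 182 and 364. Excision has mean 15 and SD 4.9. Phenolisation means run from 16 to 28; 20 and 22 are taken as values in between. The planned size is 50 per group.

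**Assumptions.** Closure times are gamma distributed with shape (mean/SD)² and scale SD²/mean. The phenolisation SD is 4.9 or 8, because the article gives none.

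**Step 1: share closing in each interval, excision.**

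- by day 7: 0.025
- day 7 to 14: 0.435
- day 14 to 42: 0.539

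So about 46% are closed by day 14 and 54% close in the gap. Normal and lognormal models put 58% and 52% in the gap.

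**Step 2: mean recorded for excision.**

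- Visit date: 7 × 0.025 + 14 × 0.435 + 42 × 0.539 = 28.9 days.
- Interval midpoint (3.5, 10.5, 28): 3.5 × 0.025 + 10.5 × 0.435 + 28 × 0.539 = 19.8 days.

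The true mean is 15.

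**Step 3: phenolisation, and the difference from excision.** Each pair is for SD 4.9 and SD 8.

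| True mean | Share in gap | Recorded mean, visit date | True difference | Difference, visit date | Difference, midpoint |
|---|---|---|---|---|---|
| 16 | 63%, 53% | 31.5, 28.6 | 1 | 2.5, -0.3 | 1.6, -0.3 |
| 20 | 90%, 75% | 39.2, 35.7 | 5 | 10.3, 6.7 | 6.5, 4.3 |
| 22 | 96%, 83% | 41.0, 38.5 | 7 | 12.1, 9.5 | 7.6, 6.2 |
| 28 | 99%, 93% | 42.2, 43.7 | 13 | 13.3, 14.8 | 8.4, 9.8 |

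Visit dates overstate the 5- and 7-day differences. Midpoints come closer there but understate the 13-day difference. Neither convention recovers the true value throughout.

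**Step 4: the test, with visit dates and 50 per group (10,000 simulated trials per scenario, lognormal and gamma).**

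- Same distribution in both arms (mean 15, SD 4.9): rejection in 5.1% to 5.4% of trials.
- Equal means of 15 but SD 4.9 against 8 or 10 (assumed): rejection in 12% to 17%.
- Both arms well inside the gap (22 against 28, SD 5, illustrative, since the article expects 15 for excision): the 6-day difference is recorded as 1.1 to 1.3 days, and power falls from 100% to 10-17%.

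**The case against.** The strongest reply is that the article never says a closed wound receives the visit date. It defines the endpoint by the actual day of epithelialisation, the form is described but not reproduced, and a condensed article may leave to the full protocol how that day is obtained. The t test is a general rule, not one named for this endpoint, and a sensitivity analysis for missing data is promised. This stands in part. It makes the size conditional on how a day is assigned, and it limits confidence to moderate. It does not remove the mismatch: the article does state a day-level definition, an assessor, a visit schedule and a single between-group rule for continuous outcomes, and these do not fit together as written.

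A reader might infer more than the document supports:

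- *That the t test will be wrong.* Its error rate stays near 5% if both arms share one closure distribution. The inflated rates need unequal spreads, which are assumed here.
- *That both means will be badly inflated.* The jump from 15 to 29 days comes from using visit dates. With midpoints it is 15 to about 20.
- *That the direction of the result may be an artefact.* Among the eight scenarios compared with excision, only the near-null one changes sign (true difference 1 day, SD 8, recorded as -0.3). The standard error of the recorded difference there is about 3 days, and exact times would still give √((4.9² + 8²)/50) = 1.3. At true differences of 5 to 13 days the direction is always kept.
- *That nearly all closures fall in the gap.* That is so for phenolisation at the higher means. For excision it is a bare majority.

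**Conclusion.** The point holds in conditional form, with moderate confidence. Unless an exact closure date is obtained between visits, this endpoint is interval-censored, and a t test on assigned days estimates something other than the mean time to closure. About 54% of excision closures and 53% to 99% of phenolisation closures would fall in the day 14 to 42 gap. True differences of 5, 7 and 13 days would be reported as about 7-10, 10-12 and 13-15 with visit dates, or about 4-7, 6-8 and 8-10 with midpoints.

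These figures rest on the gamma model, the article's means, its excision SD and an assumed phenolisation SD. The issue is confined to one secondary endpoint. The primary analysis does not depend on it.

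**What to change.** For time to wound closure, replace the t test with an interval-censored time-to-closure analysis. The interval runs from the last visit at which the wound was seen open to the first at which it was seen closed, and wounds still open are censored at the last visit. Alongside it, report the proportion closed at 2, 6 and 12 weeks by group, with risk differences and 95% confidence intervals.

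Both use data that the visits already collect. The cost is a change to the analysis wording and slightly more analysis work, with no added visits. If the full protocol or the form does capture a closure date between visits, the article should say so and say how that date is obtained.

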### Participant timeline

Patients who meet the inclusion criteria will be randomly assigned to either group A (pit excision followed by phenolisation) or group B (primary surgical excision). Patients randomised to group A are treated with excision of the sinus pit and phenolisation of the sinus tract. Afterwards, patients enter into the follow-up programme. If there is recurrent anatomic SPSD combined with symptoms interfering with daily life after at least 6 weeks, the phenolisation procedure is repeated. The treatment in group A can therefore consist of up to two phenolisation sessions. Patients randomised to group B primarily undergo excision of the sinus. Afterward, patients enter into the follow-up programme.

Data regarding quality of life and complaints related to SPSD are obtained preoperatively by questionnaires. Furthermore, the number and locations of pits of the SPSD in the natal cleft are preoperatively assessed. After the procedure, patients enter the follow-up programme. This consists of a diary during the first 2 weeks after the intervention to score complaints related to the surgical intervention, usage of pain medication and loss of days to perform normal activity and, at 1, 2, 6, 12, 26 and 52 weeks after the surgical intervention, quality of life scores, complaints in the natal cleft, satisfaction assessment and wound assessment are measured.

### Sample size

The sample size of this study was calculated based on a reduction of return to normal activity from 7.5 days in the excision group to 4 days in the phenolisation group. A more conservative estimation has been taken into account for both groups as the results shown from the literature are relatively broad (mean (SD), 9.7 (3.6) and 2.3 (3.8) days, respectively) [2,5,13]. The sample size calculation was based on α = 0.05 (two-sided) and a power of 80%. This led to a required sample size of 100 (50 per group) computed by using Microsoft Office Excel 2007 (Microsoft Corporation, Redmond, WA, USA).

### Recruitment

All patients who present to the surgical outpatient clinic of the participating centre with sacrococcygeal pilonidal sinus disease will be considered by the surgeon for participation in this research protocol. Patients with no or minimal symptoms related to SPSD are encouraged to use conservative treatment. However, if conservative treatment is inadequate or symptoms interfere considerably with daily life, there is a reason to proceed to surgical treatment. These patients are assessed if they are eligible for enrolment in this study. With 130 patients presenting with SPSD in the participating centre in 2011 and 2012, an estimation that 30% do not meet the inclusion criteria and assuming a refusal rate of 10%, the inclusion period will be about 2 years (Figure 1).

**Figure 1 Fig1:**
[figure not shown]

**Figure 2 Fig2:**
[figure not shown]
**Study protocol.**

### Blinding

Due to the nature of the intervention (that is, because of obvious differences between both interventions) neither participants nor staff members can be blinded to allocation. However, the hypothesis and the primary outcome measure are unknown to the participants.

### Data collection

Preoperatively, complaints related to SPSD (discharge, pain and itch) are evaluated and each symptom is scored by the participants on a six-point scale from 0 (no complaints) to 5 (daily complaints). Quality of life is also preoperatively measured, both by a visual analogue scale (scored from 0 (worst) to 100 (best)) and the Short Form (SF)-36 [19]. The SF-36 is a questionnaire designed to measure health-related quality of life. This questionnaire consists of 36 questions comprising eight different domains of quality of life: physical functioning, physical role limitation, emotional role limitation, bodily pain, vitality, mental health, social functioning, and general health. For each domain, a score between 0 and 100 can be obtained; the higher the score, the better the quality of life.

During the phenolisation procedure, the following items are assessed with an assessment form: number of pit excisions in midline and right and left from the midline and volume of phenol administrated in the sinus. For the excision procedure, the size and depth of the wound is measured as well as the weight of the excision specimen. For both procedures, duration of operation and possible complications are recorded.

A diary is obtained for the first 2 weeks after the intervention to score complaints related to the treatment (fluid, pain, irritation, itch, burning), scored on a six-point scale from 0 (no complaints) to 5 (daily complaints). Additionally, pain is evaluated with a visual analogue scale, scored from 0 (no pain) to 100 (extreme painful), usage of pain medication (yes or no) and if the patient is able to perform normal activity such as working or doing housekeeping work.

The postoperative questionnaire assesses the following items: patient satisfaction by the Visick satisfaction rate (disease scored by the patient as cured, improved, unchanged or worsened; the last two are considered as symptomatic recurrence) [18], symptoms related to the treatment (fluid, pain, irritation, itch, burning; scored from 0 (no complaints) to 5 (daily complaints), and quality of life as obtained by both a visual analogue scale and the SF-36 (both are assessed as described for the preoperative stage).

The wound is postoperatively assessed by an assessor with an assessment form. This form includes anatomic recurrence of SPSD, wound closure (defined as complete epithelisation of the skin) and surgical site infection scored by the Southampton wound scoring system [20]. This scoring system consists of six grades: normal healing (grade 0), normal healing with mild bruising or erythema (grade I), erythema plus other signs of inflammation (grade II), clear or haemoserous discharge (grade III), pus (grade IV) and deep or severe wound infection with or without tissue breakdown (grade V).

To encourage patients to complete follow-up, appointments are scheduled for all patients and a reminder is sent to them 2 to 3 days prior to the appointment.

All forms and questionnaires will be kept in locked cabinets and access to the study data will be restricted. All data will be entered electronically in a SPSS database (SPSS Inc., Chicago, IL, USA) and a password system will be utilized to control access and prevent unauthorised access.

### Statistical methods

The analysis in this study will be performed according to the intention-to-treat principle; that is, all participants, regardless of protocol adherence, will be analysed as randomised [21]. Continuous variable will be summarised using mean (SD) or medians (interquartile range), and binary and categorical data will be summarised using frequencies and percentages, where appropriate. Data will be analysed using SPSS for Windows version 17.0 (SPSS Inc.). We will calculate relative risk and relative risk reduction with corresponding 95% confidence intervals to compare dichotomous variables. The paired-samples *t* test will be used for statistical analysis of continuous pre- and postoperative values and the *t* test for independent samples for statistical analysis of continuous values between both intervention groups. Statistical analysis of categorical values between both groups will be performed using the Pearson Chi-square test, and statistical analysis of categorical pre- and postoperative values by the McNemar test. Differences will be considered statistically significant with *P* < 0.05. We will report reasons for withdrawal for each randomisation group. The effect that any missing data may have on results will be assessed by sensitivity analysis [21,22].

### Harms

Both surgical interventions in this study are generally accepted interventions for SPSD [5,13]. The safety of both procedures has already been established in several previous observational studies and in none of them has a serious adverse event been shown [4,6,7,11,14-16]. During the study any potential side effect or adverse event will be recorded.

